## Abstract

**Background::**

Angina pectoris of coronary heart disease is the leading cause of death worldwide. Danhong injection is a supplement for angina pectoris of coronary heart disease. A large number of studies have confirmed its efficacy and safety. However, there is no rigorous clinical study to evaluate the effects of Danhong injection on cardiac function and blood lipid in patients with angina pectoris of coronary heart disease.

**Methods::**

This is a prospective, randomized, double-blind, placebo-controlled trial to study the effects of Danhong injection on cardiac function and lipid profile in patients with angina pectoris of coronary heart disease. Participants will be randomly divided into treatment group and control group. The treatment group will be treated with Danhong injection and the control group will be treated with placebo under basic treatment according to recommended guideline, and followed up for 3 months after 14 consecutive days of treatment. Outcomes include: cardiac function (left ventricular end-diastolic diameter); left ventricular end-systolic diameter; left ventricular ejection fraction, blood lipid levels (total cholesterol; triacylglycerol; low density lipoprotein cholesterol; high density lipoprotein cholesterol), the number of angina attacks per week, total amount of nitroglycerin tablets, and adverse reactions.

**Discussion::**

This study will evaluate the efficacy of Danhong injection in improving cardiac function and blood lipid in patients with angina pectoris of coronary heart disease. The results of this study will provide reference for clinical use of Danhong injection to improve cardiac function and blood lipid in patients with angina pectoris of coronary heart disease.

Trial registration: OSF Registration number: DOI 10.17605/OSF.IO/TPZJ5.

## Introduction

1

Cardiovascular and cerebrovascular diseases are the main causes of death worldwide.^[1]^ According to WHO statistics, 17.9 million people died of cardiovascular diseases worldwide in 2016, accounting for 31% of the total global deaths, among which about 34% died of coronary heart disease.^[2]^ Coronary heart disease has become 1 of the diseases with the highest mortality rate in human beings and seriously endangers human physical and mental health.^[1]^ Angina pectoris of coronary heart disease is a syndrome caused by acute myocardial ischemia and anoxia,^[3]^ its pathogenesis is complex and generally related to epicardial coronary artery stenosis caused by atherosclerosis, reducing the coronary circulation of myocardial blood supply. And coronary microcirculation, imbalance between myocardial oxygen supply and metabolic oxygen demand are also important influence factors. Its molecular mechanism may involve vascular endothelial function, immune inflammation, thrombosis, lipid metabolism, oxidative damage, and other factors.^[4]^

At present, drug therapy for angina pectoris of coronary heart disease includes nitrates, calcium antagonists, antiplatelet aggregation, drugs that improve myocardial metabolism, drugs that stabilize atherosclerotic plaques and β-blockers, etc.^[5]^ Although some drugs take effect fast and the curative effect is distinct, but in the face of angina pectoris of coronary heart disease, which is a multi-pathway and multi-gene complex disease, the drugs still exist certain limitations.^[6]^ And clinical studies have found that traditional anti-myocardial ischemia therapy does not reduce cardiovascular adverse events, there are still 5% to 15% of patients with refractory angina pectoris attack.^[6,7]^

Traditional Chinese medicine has the characteristics of multi-target and multi-link, especially in the treatment of cardiovascular diseases with a long history, and its efficacy and safety have been widely studied and verified.^[8]^ Traditional Chinese medicine treatment schemes vary with different pathogenesis. Blood stasis syndrome is usually the main pathogenesis of angina pectoris of coronary heart disease, so activating blood circulation and removing blood stasis is a very important therapeutic goal.^[9]^ Danhong injection, consisting of Dan Shen and Hong Hua, is a traditional Chinese medicine injection based on promoting blood circulation and removing blood stasis, which is widely used in the treatment of cardiovascular diseases in China,^[10]^ and strongly recommended in *the Clinical Application Guide of Chinese Patent Medicine in treating Coronary Heart Disease (2020)*.^[11]^ Pharmacological studies have found that Danhong injection has effects of anti-inflammatory, antioxidant, anticoagulant, lipid-lowering, anti-apoptosis, vasodilation, and angiogenesis promotion.^[12]^ Clinical studies have confirmed that Danhong injection can relieve angina symptoms and improve electrocardiogram.^[13]^ Although current studies have confirmed the effectiveness and safety of Danhong injection in the treatment of angina pectoris of coronary heart disease,^[14]^ there is no study on the effect of Danhong injection on the cardiac function and blood lipid of the limbs affected by angina pectoris of coronary heart disease. The changes of cardiac function and blood lipid in patients with angina pectoris of coronary heart disease are of great significance to evaluate the prognosis of patients, which can also reflect the long-term efficacy of drugs. This study will explore the effects of Danhong injection on cardiac function and blood lipid in patients with angina pectoris of coronary heart disease in a prospective, randomized, double-blind, placebo-controlled trial.

## Materials and methods

2

### Study design

2.1

This is a prospective, randomized, double-blind, placebo-controlled study of the effects of Danhong injection on cardiac function and lipid profile in patients with angina pectoris of coronary heart disease. Participants will be randomly divided into treatment group and control group, the treatment group will receive Danhong injection treatment, and the control group will receive placebo treatment. The patients will be followed up for 3 months after 14 days of continuous treatment. Flow diagram is shown in Figure 1, study schedule is shown in Table 1. This protocol followed the latest Consolidated Standards of Reporting Trials 2017 and Standard Protocol Items: Recommendations for Interventional Trials 2013 statement.

**Figure 1 F1:**
[figure not shown]
Flow diagram of this clinical trial.

**Table 1 T1:** Study schedule.

	Screening period	Treatment period		Follow-up		
--Project Stage	Baseline	1-wk	2-wk	1-mo	2-mo	3-mo
Record fill	√					
Fulfill inclusion criteria and exclusion criteria	√					
Sign informed consent	√					
Random allocation	√					
Treatment	√	√	√			
Effectiveness observation						
Cardiac function	√		√			√
Blood lipid levels	√		√			√
The number of angina attacks per week	√	√	√	√	√	√
Total amount of nitroglycerin tablets	√		√			√
Safety evaluation						
Blood test and urinalysis	√		√			√
Liver and kidney function	√		√			√
Record of adverse event		√	√	√	√	√

### Ethics and registration

2.2

This Research protocol will be conducted in accordance with Declaration of Helsinki and Ethical Guidelines for Clinical Research. This study has been approved by our Clinical Research Ethics Committee and has registered in open science framework (registration number: DOI 10.17605/OSF.IO/TPZJ5). Before randomization, all patients were required to sign an informed consent form, giving them the option of continuing the trial at any time.

### Patients

2.3

#### Diagnostic basis

2.3.1

The diagnostic criteria for angina pectoris of coronary heart disease refers to *Nomenclature and criteria for diagnosis of ischemic heart disease*.^[15]^ The diagnostic criteria of TCM diseases and syndromes refers to *Diagnostic and therapeutic criteria of traditional Chinese medicine diseases*.^[16]^

#### Inclusion criteria

2.3.2

Patients who meet the diagnostic basis of angina pectoris of coronary heart disease, and meet the requirements of coronary angiography or coronary angiography that there is at least 1 coronary artery stenosis with catheter stenosis ≥50%, and whose myocardial ischemia and ECG ST-T changes are confirmed by cardiac MRI or radionuclide myocardial perfusion imaging.Patients whose age ≥18 years, and ≤70 years;Patients who agree to participate in this study and signed informed consent.

#### Exclusion criteria

2.3.3

Patients who have severe mental illness, severe cardiopulmonary insufficiency, severe arrhythmia, or other serious illness (such as tumor);Patients whose ALT, AST or Cr reaches 1.5 times of normal upper limit^[17]^;Patients who have other diseases that may increase the risk of bleeding, such as a history of bleeding in vital organs (such as cerebral hemorrhage and upper gastrointestinal bleeding), reduced platelet count, abnormal coagulation function, and recent active bleeding within the last 6 months;Women who are pregnant, preparing to pregnant or breastfeeding;Patients who are allergic to the drugs used in the study;Patients who have participated within the last 1 month or are currently participating in other clinical trials.

#### Shedding criteria and management

2.3.4

Patients who appear severe adverse events or other complications and special physiological changes. The trial should be stopped and corresponding treatment should be given according to the judgment of the investigator;If the subject's condition does not improve or even deteriorate to a certain extent within a certain period of time, although the required follow-up had not been completed, the subject should be withdrawn from the study and received other effective treatments in order to protect the subject;Patients who have poor compliance, change medications or add non-prescribed medications, which may affect the result of the study;Patients who are unwilling or impossible to continue the clinical trial for any reason, and suspend the test by requesting the investigator to withdraw from the test;Patients who are misdiagnosed, or accidentally included without meeting the inclusion and exclusion criteria.

For patients who dropped out of the trial or lost to follow-up, researchers should take active measures to complete the last test as far as possible, so as to analyze its efficacy and safety, and take corresponding treatment measures. All shedding cases should be recorded on the case report form (CRF), and filled in the cause.

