### Statistical analysis

2.10

Efficacy evaluation will be determined by full analysis set and per-protocol set, and safety evaluation will be based on safety set. Statistical evaluation of full analysis set will follow intent-to-treat principles. Last observation carried forward method was used to estimate missing values of major variables. The collected data were statistically analyzed by SPSS 22.0 software. Chi-square test was used for enumeration data; mean value ± standard deviation ($\bar{\text{x}}$ ± S) was used for measurement data, independent sample *t* test was used for normal distribution, and Mann-Whitney *U* test was used for skewed distribution. When *P* < .05, the difference was considered statistically significant.

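### Withdrawing non-improving patients from the study before follow-up ends makes later outcomes missing in a response-dependent way, in tension with the intent-to-treat full analysis set

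*Protocol article*

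**What the plan says.** **Protocol article, section 2.3.4 (Shedding criteria and management).** The section lists reasons for a patient to leave after entry.

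- *Lack of response.* For a subject whose condition "does not improve or even deteriorate to a certain extent within a certain period of time", the instruction is that "the subject should be withdrawn from the study and received other effective treatments in order to protect the subject", and the text makes clear that this applies with follow-up still outstanding. The extent and the period are not specified.
- *Severe adverse events, complications or special physiological changes.* The trial is to be stopped for the patient, on the investigator's judgement.
- *Compliance and medication.* "Patients who have poor compliance, change medications or add non-prescribed medications, which may affect the result of the study".
- *Eligibility errors.* "Patients who are misdiagnosed, or accidentally included without meeting the inclusion and exclusion criteria".
- *The patient's own wish or inability to continue.*

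For dropouts and patients lost to follow-up, "researchers should take active measures to complete the last test as far as possible, so as to analyze its efficacy and safety". Each case and its cause go on the case report form.

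**Section 2.10 (Statistical analysis).** Efficacy is assessed in two populations, the full analysis set and the per-protocol set; safety has its own set. For the first of these the plan states: "Statistical evaluation of full analysis set will follow intent-to-treat principles". Gaps in the major variables are filled by last observation carried forward (LOCF).

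**Table 1 (Study schedule).** Cardiac function, lipids and nitroglycerin use are recorded at baseline, week 2 and month 3. Weekly angina attacks are recorded at baseline, weeks 1 and 2, and months 1, 2 and 3.

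**The concern.** An intent-to-treat comparison needs outcomes on randomized patients whatever their response, compliance or later eligibility finding. Section 2.3.4 ends follow-up because of how the patient is doing, so the plan itself creates missing data that depend on the outcome. Because the threshold is undefined, its application rests on judgement and may vary between patients.

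Two things are at stake. The full analysis set would hold carried-forward values where the later outcomes of poor responders should be. The per-protocol set, if it is confined to patients who were not shed, would be filtered on response, which is itself affected by treatment. An analysis plan can choose a better method for missing values, but it cannot recover visits that did not take place.

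**Working it through.** **1. What is missing, and when.** Setting section 2.3.4 beside Table 1 and the LOCF rule in section 2.10 gives, for LVEF and lipids:

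| Time of withdrawal | Last test obtained? | Week-2 value used | Month-3 value used |
|---|---|---|---|
| Before the week-2 assessment | No | Baseline carried forward | Baseline carried forward |
| Before the week-2 assessment | Yes, at exit | Exit value at best | Exit value carried forward |
| After the week-2 assessment | No | Observed | Week-2 value carried forward |
| After the week-2 assessment | Yes, at exit | Observed | Exit value carried forward |

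Month 3 is therefore the main exposure. The day-14 LVEF, on which the sample size rests, is exposed chiefly where a patient leaves before the week-2 echo and the last test is missed. The table takes the last test to be one assessment on leaving; the other reading is discussed under the objection.

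**2. The plan's own figures (section 2.4).** LVEF at day 14 is 53.13 ± 6.18 versus 49.78 ± 5.78, with one-sided α = 0.025 and β = 0.20.

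- Difference: δ = 53.13 − 49.78 = 3.35.
- Pooled SD: σ = √[(6.18² + 5.78²)/2] = 5.98.
- n per group = 2σ²(1.960 + 0.842)²/δ² = 50.1, rounded up to 51. The stated 49 is within two patients of this.
- Drop-out: 49/0.90 = 54.4, rounded up to 55, as stated.

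These inputs are sound enough to use for an illustration.

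**3. Illustration for completers only.** The assumptions, none of which is in the document, are: LVEF normal in each arm with common SD 5.98, true difference 3.35, and removal of everyone below one fixed LVEF cut-off, set so that it removes a fraction p of controls.

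- Control cut-off in SD units: z_C = Φ⁻¹(p). Treated: z_T = z_C − δ/σ = z_C − 0.560.
- Fraction of treated removed: Φ(z_T).
- The mean of those left rises by σ·h(z), where h(z) = φ(z)/[1 − Φ(z)].
- Difference among those left: δ + σ[h(z_T) − h(z_C)].

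| p (controls removed) | z_C | z_T | Treated removed | h(z_C) | h(z_T) | Difference left |
|---|---|---|---|---|---|---|
| 10% | −1.282 | −1.841 | 3.3% | 0.195 | 0.076 | 3.35 − 5.98 × 0.119 ≈ 2.64 |
| 20% | −0.842 | −1.401 | about 8% | 0.350 | 0.162 | 3.35 − 5.98 × 0.187 ≈ 2.23 |

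Averaged over the arms, removal is about 6.7% in the first case, (10 + 3.3)/2, and about 14% in the second, (20 + 8)/2. The document allows 10% drop-out from all causes, so the first case fits within that allowance and the second does not.

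**4. What this does not show.** The calculation truncates day-14 LVEF values, whereas section 2.3.4 speaks of the patient's condition in general. It describes only those who remain, so it bears on a completers or per-protocol comparison. It measures neither the LOCF-based full analysis set nor month 3.

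**The case against.** A reader might infer that shed patients are dropped from the full analysis set, so that section 2.3.4 flatly contradicts section 2.10. The documents do not support that. Nothing removes shed patients from the full analysis set. The last-test sentence shows that dropouts are meant to be analysed, and LOCF can keep every randomized patient in. Leaving follow-up is not the same as leaving the analysis set. This objection stands: the conflict is a tension over data collection and an ambiguity over set membership.

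A reader might also take every listed ground as a removal from the study. Express withdrawal with follow-up incomplete is stated only for patients who do not improve or who deteriorate. For adverse events the text says the trial is to be stopped. Poor compliance, medication change and ineligibility are merely listed, and they are ordinary reasons to leave a patient out of a per-protocol set. This also stands.

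The last test could mean the final scheduled assessment rather than an exit visit. That reading is possible and would reduce the loss at month 3. But the request is only as far as possible, and it does not cover the other assessments still due.

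The patients and the principal investigator are blinded (section 2.5), which limits deliberate withdrawal by arm. It does not remove dependence on response: if one arm does worse, more of its patients meet the rule.

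Finally, an article may leave the detail of analysis sets to a fuller document. That covers how the sets are defined. It does not cover an instruction, stated here, that ends follow-up on account of response.

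**Conclusion.** The concern holds in a limited form. As written, section 2.3.4 makes later outcomes missing in a way that depends on response, chiefly at month 3, and at day 14 for patients withdrawn before the week-2 echo without a last test. LOCF fills these gaps but does not repair them. The per-protocol set is open to selection on response.

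Neither the size nor the direction of the bias can be fixed from the document, because the rule is undefined and both the withdrawal rate and the last-test completion rate are unknown. A fall from 3.35 to about 2.6 or 2.2 LVEF points is an illustration for completers under the assumed cut-off. A reader might take it as a forecast of dilution in the main analysis, which it is not. Withdrawals driven by adverse events in one arm, for example, could shift the comparison either way.

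**What to change.** Leave the investigator's decisions on treatment exactly as written, and change the wording on follow-up and analysis:

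1. In section 2.3.4, separate stopping study treatment from leaving the study.
2. State that every randomized patient who has not withdrawn consent keeps the remaining Table 1 assessments (week 1, week 2, and months 1, 2 and 3, as applicable), with treatment changes recorded.
3. State that these patients, including non-improvers and those later found ineligible, stay in the full analysis set in their randomized arm.
4. Use compliance, medication and eligibility deviations only to define the per-protocol set.

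The change uses visits already in Table 1. Its cost is protocol wording, with the ethics re-approval that section 2.9 requires for any change, and a small extra effort to keep seeing patients who stopped the infusion. It should be made before patients are withdrawn, because the missed assessments cannot be recovered afterwards.

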### Sample size

2.4

The sample size was estimated based on the mean and standard deviation of the left ventricular ejection fraction (LVEF) scores of patients 14 days after treatment. Based on the results of the preliminary experiment, the LVEF score was 53.13 ± 6.18 in the treatment group and 49.78 ± 5.78 in the control group. α = 0.025, one-tailed test, β = 0.20. The PASS15.0 software calculated that 49 participants were required for each group, with an estimated drop-out rate of 10%, 55 patients would be enrolled in each group.

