### Randomization and blinding

2.5

Patients meeting the criteria would be randomly assigned to treatment group (Danhong injection group) or control group (placebo group) in a 1:1 ratio through a randomization tool based on a central network. Random sequences were generated using SAS 9.3 software (SAS Institute, Cary, NC) by independent statisticians that were not involved in trial implementation or statistical analysis. The research assistant entered patient information on a tablet computer and was assigned a random number to complete the random assignment. The outcome of the assignment was unknown to the patients and principal investigator throughout the study. Because Danhong injection was different from 0.9% normal saline in color, we used opaque brown bag to seal the infusion bottle and used brown infusion set for infusion. A professional nurse prepared the medication in a dedicated infusion room and sealed the infusion bottle in a brown bag with only the patient's number on it, another nurse was responsible for completing the infusion according to the number. These programs would be implemented by 2 professional nurses, and they would be asked to sign a confidentiality agreement before the start of the study without being in contact with each other.

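### Section 2.4's inputs call for 52 evaluable patients per group, not 49; at 49 the power is about 78%, not 80%, a small shortfall that needs restating, not more patients

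*Protocol article*

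**What the plan says.** Section 2.4 (Sample size) bases the calculation on LVEF at a 14-day time point. It takes its planning values from a preliminary experiment: "the LVEF score was 53.13 ± 6.18 in the treatment group and 49.78 ± 5.78 in the control group". The error rates are "α = 0.025, one-tailed test, β = 0.20". The result reads: "The PASS15.0 software calculated that 49 participants were required for each group, with an estimated drop-out rate of 10%, 55 patients would be enrolled". Both numbers are per group.

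Section 2.5 (Randomization and blinding) allocates patients "in a 1:1 ratio through a randomization tool based on a central network".

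Section 2.10 (Statistical analysis) plans an independent-sample t test for normally distributed measurements and a Mann-Whitney U test for skewed ones. Efficacy is analysed in the full analysis set, on intent-to-treat principles, and in the per-protocol set. Missing values of major variables are filled by last observation carried forward. At P < .05, "the difference was considered statistically significant"; the section does not say whether P is one- or two-sided.

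**The concern.** Section 2.4 prints every input needed to recompute the sample size and names the software that produced it. A reader should therefore be able to get 49 back, and cannot. Either an input is misprinted or the 49 is not the right output for these inputs, and only the sponsor can tell which.

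What is at stake is the stated 80% power. It is the figure by which a non-significant LVEF result will be judged, so it should be true of the number it is attached to.

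**Working it through.** **Inputs (section 2.4, with 1:1 allocation from section 2.5)**
- Difference: 53.13 − 49.78 = 3.35
- Variances: 6.18² + 5.78² = 38.19 + 33.41 = 71.60
- Common SD (root mean square): √(71.60/2) = 5.983
- Standardised difference: 3.35/5.983 = 0.560
- One-sided α = 0.025 (z = 1.960); power 0.80 (z = 0.842)

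**Step 1. The drop-out inflation, which reproduces.** 49/(1 − 0.10) = 54.4, rounded up to 55. In the other direction, 55 × 0.9 = 49.5.

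**Step 2. Normal approximation, the most lenient method.**
n = (1.960 + 0.842)² × 71.60 / 3.35² = 50.08, so 51 per group.
Power at 49: Φ(0.560 × √(49/2) − 1.960) = Φ(2.771 − 1.960) = Φ(0.811) = 79.1%.

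**Step 3. The planned t test (noncentral t, noncentrality 0.560 × √(n/2), 2n − 2 degrees of freedom).**

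| Per group | Power |
|---|---|
| 49 | 78.3% |
| 50 | 79.2% |
| 51 | 79.96% |
| 52 | 80.7% |
| 55 | 82.9% |

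The first n to reach 80% is 52. The unequal-variance (Welch) version also gives 52, and 78.3% at 49. At 51 the power misses 80% only in the second decimal. Using the plain average of the two SDs (5.98) gives 51 instead.

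**Step 4. Is there a reading of the inputs that gives 49?**

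| Variant | Normal approx. | t test |
|---|---|---|
| SD 5.78 for both groups | 47 | 48 |
| SD 6.18 for both groups | 54 | 55 |
| Average SD 5.98 | 51 | 51 |
| α 0.05 one-sided | 40 | 41 |
| α 0.025 two-sided | 61 | 62 |

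None gives 49. Rounding the difference to 3.4 in the normal formula would: (1.960 + 0.842)² × 71.60 / 3.4² = 48.6, so 49. That is an assumption, because the protocol reports no such rounding.

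**Step 5. Enrolment that 80% at the evaluable count would imply.** 52/0.9 = 57.8, so 58 per group; by the normal approximation, 51/0.9 = 56.7, so 57. The protocol has 55.

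**Step 6. Section 2.4 against section 2.10 on α.** One-sided 0.025 and two-sided 0.05 give the same t-test answers: 52 per group, and 78.3% power at 49.

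**The case against.** **The gap is trivial for a calculation based on pilot data.** This largely stands. With 49 per group, 80% power is reached if the true difference is 3.42 instead of 3.35, or if the SD is 5.86 instead of 5.98. Either lies well within the uncertainty of a preliminary experiment. That limits the importance of the error. It does not make the printed 49 follow from the printed inputs.

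**The trial enrols 55, and efficacy is analysed in the full analysis set.** This also stands. If all 55 per group contribute, nominal power is 82.9%, above the 80% stated. A reader might infer from 78% that the trial is materially underpowered; the document does not support that. The 82.9% is, however, a nominal figure. Under the schedule in Table 1, cardiac function is measured at baseline and week 2 during treatment, so a missing week-2 LVEF would be filled with the baseline value. That could dilute the difference.

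**A reader might see a conflict between one-tailed 0.025 in section 2.4 and P < .05 in section 2.10.** There is none if P is two-sided, the ordinary reading: in the favourable direction the two rules are the same criterion. The favourable-direction error would double, from 2.5% to 5%, only if a one-tailed P were set against .05, and section 2.10 does not say that. Unstated sidedness is a missing detail of the kind an article may leave to the full plan.

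**A reader might also suppose that the Mann-Whitney fallback widens the gap.** The usual efficiency loss against the t test is derived for normal data. Section 2.10 keeps the rank test for skewed data, where that figure does not apply and the rank test can be the more efficient of the two. No further shortfall follows from the document.

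**Conclusion.** The statement that 49 evaluable patients per group are required for 80% power is wrong on the protocol's own inputs. The planned t test needs 52, and the normal approximation needs 51. The shortfall is 2 to 3 evaluable patients per group, or 1.7 power points by the t test (78.3%) and 0.9 by the normal approximation (79.1%).

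This is a small error, confined to the sentence about 49 evaluable patients. The inflation to 55 is correct, and with all 55 per group analysed nominal power is about 83%. It shows neither a materially underpowered trial nor a wrong significance level.

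The result assumes that the means and SDs are printed correctly, that the comparison is of 14-day LVEF between two equal groups, and that LVEF is close enough to normal for the t test. If an input is misprinted, the 49 may be right and the input is what needs correcting. The document does not settle which.

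**What to change.** Do not enrol more patients. Recheck the PASS 15.0 output behind section 2.4, then do one of two things:

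1. If a mean, SD or error rate was misprinted, correct it so that 49 can be reproduced, and name the PASS procedure used.
2. If the inputs are right, restate the result along these lines: *49 evaluable patients per group give about 78% power (one-sided 0.025, equivalent to two-sided 0.05) to detect a difference of 3.35 points in LVEF with an SD of about 5.98; if all 55 enrolled per group are analysed, power is about 83%.*

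As an optional clarification, write *two-sided P < .05* in section 2.10, so that the match with one-sided 0.025 in section 2.4 is explicit.

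The cost is one or two sentences and, in the second case, a stated power slightly below 80% for the evaluable count. Enrolment, conduct and the planned tests do not change.
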